| The risk anticipated for the patients are:  1. All research techniques and medications have potential dangers and adverse effects. Blood collection may result in discomfort, bleeding, bruising, or swelling where the needle was inserted. Fainting may occur, and infections happen infrequently.  2. Allergic reactions can occur with any drug such as rash, itching etc.  3. Rarely, a severe and possibly life-threatening allergic reaction can occur. Symptoms of a severe reaction include: swelling of the face, difficulty breathing, or a sudden drop in blood pressure that may cause dizziness.  4. For the study drugs, there are some side effects that are unique to the drugs (prednisolone and methotrexate).  i) Prednisolone may cause mood changes (confusion, depression), weight gain, fluid retention, nausea, vomiting, indigestion, easy bruising, blood or black, tarry tools, blurred vision, increased urination or thirst, muscle weakness or cramps and severe stomach pain.  ii) Methotrexate may cause mouth ulcers, nausea, vomiting, abdominal pain, diarrhoea, rash, hair loss, easy bruising, severe sore throat, tiredness, paleness, yellow eyes, tea-coloured urine, constant abdominal pain, risk of infection and breathlessness or persistent dry cough. |  |
| **STUDY POPULATION** |  |
| List the number of subjects to be enrolled |  |
| 40 IGM patients, aged between 21 to 60 years will be recruited from NUH. |  |
| Criteria for Recruitment |  |
| Patients must have undergone biopsy and diagnosed with IGM. Eligible patients will be informed by their attending healthcare professional on the study during the clinic session. If patient is interest to join the study, a qualified study team member will then explain the study and obtain informed consent from the patient. Before beginning any study-related procedures, informed consent will be obtained. Patient will then be assigned a participant study code and randomised to a treatment arm. Recruitment will be done face-to-face in NUH at Breast Care Centre. |  |
| Inclusion Criteria |  |
| Patients will have to meet all of the following criteria below:   - Women, aged between 21 and 60 years - Positive diagnosis of idiopathic granulomatous mastitis based on histopathology results - Willing and able to give informed consent |  |
| Exclusion Criteria |  |

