| This is a prospective pilot randomised trial to study the effectiveness of prednisolone versus methotrexate in achieving clinical or radiological complete response for women with IGM. Patient will be recruited from NUH and written informed consent will be obtained prior to screening and enrolment. Patient will be randomised to one of the treatment arms.  The 2 arms consist of:   - Control arm (20 patients):   - Prednisolone tablet will start at 20mg daily for first 2 weeks (Refer to Figure 2 for tapering doses) with 20mg of omeprazole daily (Refer to Section 8.6) - Experimental arm (20 patients):   - Methotrexate tablet will start at 10mg once a week for the first month (Refer to Figure 2 for increasing of dosage) with 5mg of folic acid (Refer to Section 8.6) |  |
|  |  |
| **METHODS AND ASSESSMENTS** |  |
| Randomisation and Blinding |  |
| Permuted block randomisation will be performed with randomly varying block sizes of 4 and 6. Eligible and consented participants will then be randomly assigned to either of the treatment arm based on their baseline visit date. |  |
| Contraception and Pregnancy Testing |  |
| We do not accept women who self-report or test as pregnant during recruitment. |  |
| Study Visits and Procedures |  |
| **Study Visits and Procedures** |  |

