| *Screening*  After patient is consented to the study, a baseline blood test (32mls, including pregnancy test, Hepatitis B test, Hepatitis C test, full blood count, liver function test and renal function test) and chest X-Ray will be conducted during the baseline visit to assess for eligibility prior to enrolment to the treatment phase. Additional research blood (14.5mls, 1 tablespoons) will be collected at this baseline visit for research purposes. Patient may be exempted from chest X-Ray and/or blood test if patient has done the same test within 30 days.  Baseline demographics and relevant clinical variables of patients will be collected. The following demographic and clinical variables will be collected: age of presentation, pre-menopausal or post-menopausal status, parity / breastfeeding status, concomitant rheumatic conditions, personal or family history of tuberculosis, smoking or alcohol intake, presenting complaint, unilateral or bilateral involvement, affected quadrant of the breast, duration of symptoms and previous antibiotics prescription for treatment of IGM.  Information on comorbidities will be evaluated to ensure suitability for both treatment arms prior to recruitment. Examples include drug allergies, plans for pregnancy, ongoing infection, previous history of cancer, previous tuberculosis, epilepsy, diabetes, hypertension, kidney, liver, cardiac problems, osteoporosis, glaucoma, peptic ulcers, previous side effects to either prednisolone or methotrexate.  If patient fulfilled all the eligibility criteria after screening assessment, she will be randomised to either of the treatment arm.  If patient did not meet the full eligibility criteria (eg. Pregnant, hepatitis carrier or abnormalities in renal or liver panels), she will not proceed to the treatment phase. The data collected and additional blood samples will be kept for analysis.  *Treatment Phase*  Patient will be scheduled to attend a clinical visit (T_0_) to either breast or rheumatology clinic if she meets all eligibility criteria for the initiation of treatment dose. There will be a window period of ± 7 days for this clinical visit. Patient is required to complete a pre-treatment quality of life online survey (approximately 10-15 minutes).  Patient will be scheduled for blood test (8mls, 0.5 tablespoons) and clinical visits to either breast or rheumatology clinic at the 1^st^ (T_1_), 2^nd^ (T_2_), 3^rd^ (T_3_) and 6^th^ (T_4_) month to assess their signs and symptoms, and drug compliance. There will be a window period of ± 14 days for each of these clinical visits. Additional research blood (14.5mls, 1 tablespoons) will be collected on the 1^st^ (T_1_) and 6^th^ (T_4_) months.  Patients are required to undergo a breast ultrasound to assess for their radiological response during the 3^rd^ (T_3_) clinical visit. A window period of ± 14 days will be applicable. The initial measurement of the breast lesion or mass will be recorded in three dimensions – i.e. anteroposterior, superior-inferior, mediolateral measurements. If complete clinical and radiological complete response has been achieved on the 3^rd^ (T_3_) visit, the doctor will discontinue the drug in a safe manner and no further breast ultrasounds will be required. If the patient’s symptoms or signs have not resolved by the 3^rd^ (T_3_) clinical visit, patient’s drug dosage will be assessed by the rheumatologist and treatment may be continued up to the 6^th^ (T_4_) month period and a repeat breast ultrasound will be required at the 6^th^ (T_4_) month. If symptoms have not resolved by the 6^th^ (T_4_) month of clinical visit, the patient’s drug dosage may be up-titrated or will be given an addition of a second therapy, i.e. combination therapy of steroid and methotrexate may be used. For clinical visits mention above, it will coincides with standard care visit.  During the clinical visits, Tingting Hu et al’s “M- score” will be adopted to grade the severity of the disease. M score is being calculated during clinical visits for IGM patients regardless of trial status for objective follow up. This is a common practice. For this study, the score will be administered by their attending healthcare professional (not limited to breast surgeons, investigators, or breast care nurses).  The M-score will be the sum of the following:  1) Mass score  2) Erythema score  3) Fistula score  4) Pain score  5) Quality-of-life (QoL) score  The scoring criteria were defined as follows:  1) Mass score: 0 for the absence of mass by palpation; 1 for mass ≤3 cm by palpation; 2 for mass >3 cm by palpation.  2) Erythema score: 0 and 2 for the absence and presence of erythema, respectively  3) Fistula: 0 and 2 for the absence and presence of fistula, respectively  4) Pain Score: 0 for Visual Analogue Score (VAS) 0-2; 1 for VAS 3-5; 2 for VAS 6-10  5) QoL score: 0 for absence of effects on QoL; 1 for mild effects on QoL, where the patient does not require medical assistant; 2 for serious effects on QoL, where the patient requires medical assistant  The total M-score ranges between 0 and 10 and serves as a quantitative and objective measurement of the severity of the symptoms.  The primary endpoint will be the clinical complete response (cCR) rate, which is defined as the proportion of patients who have an M-score of ≤ 1 at ≤1 years after treatment.  The secondary endpoints will be as follows:   - - The time to cCR, defined as the median time to cCR post randomisation.   - The treatment failure (TF) rate, defined as the proportion of patients with TF at 1 year post randomisation. The TF status will be defined as follows:     - If the patient has an M-score ≥6 before randomisation, TF is defined as the M-score remaining at ≥6 at 1 month post randomisation.     - If the patient has an M-score between 4 and 5 before randomisation, TF is defined as the M-score remaining at ≥4 and never being lower than 4.     - If the patient has an M-score <4 at baseline but never reaches cCR after randomisation, TF is defined as the M-score being >5 at the follow-up and remaining above 5 for one month. - Relapse rate, which is defined as the proportion of patients who have M-score >4 among the patients who achieved CR.   Throughout the course of the study, there are possible flares and relapse of the disease. Flares will be defined as any increase in M-score or lesion size on ultrasound whilst on therapy. While relapse will be defined as recurrence of symptoms or signs of IGM in the breast after previously experiencing complete resolution following therapy. If relapse occurs, patient will restart the same treatment arm for 6 months.  In the event of flares, blood test (8mls, 0.5 tablespoons) and additional research blood (14.5mls, 1 tablespoons) will be collected and the allocated treatment for the patient will be up-titrated by the doctor. In event of relapse, treatment for the patient will be reinitiated as per the allocated arm.  Additional research blood samples collected during the trial will be used for gene expressing profiling to identify unique patterns of gene expression that can be used to diagnose IGM and predict its treatment response.  Regardless of treatment arm, patient will be monitored by either breast surgeon or rheumatologist. Surgeons will assess for eligibility into trial, clinical reviews, and ultrasound breasts interpretation. Rheumatologists will be monitoring for drug side effects and titration if required. In event of failure of medical therapy, surgeons will have to intervene accordingly for aspiration or surgical drainage. In the event where patients require aspiration or surgical drainage during the study, methotrexate or prednisolone should be continued unless there is evidence of sepsis. The frequency of aspiration or surgical intervention will be recorded as events during the study.  Whenever the disease has been resolved during the study period, the balance medication and/or packaging will be retrieved to do medication accounting and checking for adherence to assigned treatment arm.  If side effects were to develop, doctors will evaluate the severity of the side effects and withdraw the patients from the trial if needed. |  |

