| During the course of the study, patients on both treatment arms will be instructed to/advised:   1. Not get pregnant or try to get pregnant 2. No breastfeeding 3. Avoid alcohol 4. Inform the PI/Site PI/doctor before getting any vaccinations during study period 5. Strictly refrain from concurrent dosing with other medicines, including prescriptions, and to inform the investigator(s) immediately about any new medication they need/want to take 6. Take medication as per packaging instructions   For patients on methotrexate, an additional instruction of not consuming tolbutamide and/or co-trimoxazole will be given, due to possible drug interactions. |  |
| Blinding |  |
| This is a prospective pilot open label randomised trial. Patients and study team will not be blinded with regards to the treatment assigned. |  |
| Concomitant therapy |  |
| 20mg/day of omeprazole tablet will be taken with prednisolone tablet to reduce the irritation to the stomach caused by prednisolone.  5mg of folic acid tablet will be taken with methotrexate tablet every week to reduce bone marrow suppression. |  |
| **SAFETY MEASUREMENTS** |  |
| Definitions |  |
| Prednisolone and methotrexate have been widely used in local clinics for various diseases.    Prednisolone can be used to help reduce inflammation and reduce symptoms of swelling, redness and itchiness. It has been widely used to treat various diseases such as asthma, allergic conditions, skin problems, etc. It is also the standard of care treatment given to IGM patients in NUH and has a good safety profile.  Methotrexate is commonly used by rheumatologists for treatment of autoimmune diseases such as rheumatoid arthritis, systemic lupus erythematosus (SLE), etc.  Adverse events will be reported according to Common Terminology Criteria for Adverse Events (CTCAE) Version 5.0. |  |
| Collecting, Recording and Reporting of “Unanticipated Problems Involving Risk to Subjects or Others” – UPIRTSO events to the NHG Domain Specific Review Boards (DSRB) |  |

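### Assignment is tied to the screening-visit date without saying how, and sections 3.2 and 6.3 disagree on whether randomisation precedes confirmed eligibility

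*Protocol*

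**What the plan says.** Section 6.1 (Randomisation and Blinding) has two sentences. The first sets how the sequence is generated: "Permuted block randomisation will be performed with randomly varying block sizes of 4 and 6". The second links patients to it: "Eligible and consented participants will then be randomly assigned to either of the treatment arm based on their baseline visit date". Neither names a list holder, a concealment step or the moment at which an allocation is released.

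Section 3.2 (Criteria for Recruitment) describes consent, "Before beginning any study-related procedures, informed consent will be obtained", and goes on: "Patient will then be assigned a participant study code and randomised to a treatment arm". It mentions no screening tests between the two.

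Section 6.3 (Study Visits and Procedures, Screening) says the blood tests and chest X-ray "will be conducted during the baseline visit to assess for eligibility prior to enrolment to the treatment phase". It then states: "If patient fulfilled all the eligibility criteria after screening assessment, she will be randomised to either of the treatment arm". Figure 1 also places the baseline time point in the screening phase.

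Section 8.5 (Blinding) adds: "Patients and study team will not be blinded with regards to the treatment assigned". Section 3.2 gives one recruiting clinic. Section 6.3 gives surgeons the eligibility assessment, the clinical reviews and the reading of the breast ultrasounds. Section 11.2 makes intention-to-treat the primary analysis.

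**The concern.** A random sequence protects a trial only if nobody who decides on entry can know or influence the next arm. A calendar date is a poor link between patient and sequence, because it is visible to everyone and can be moved. This date is also set before the hepatitis, pregnancy, renal and liver results are in.

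Two harms are possible. First, if the date points to a place on a list that recruiting staff can see, the arm is known while eligibility is still being decided. Some of those decisions need judgement, such as whether a concomitant medicine is a contraindication or whether comorbidities suit both arms. Second, if randomisation follows consent directly, as section 3.2 reads, patients who then fail screening have already been allocated. Whether they belong in the intention-to-treat set is unclear, the more so because section 6.3 keeps the data of screen failures for analysis. Analysis of 40 patients could not reliably repair selection at entry.

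**Working it through.** The protocol states no figure on this point, so the check is a comparison of its sections.

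**Step 1. When is the baseline visit?** Figure 1 and section 6.3 agree that it is the screening visit. The date named in section 6.1 therefore exists before eligibility is settled.

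**Step 2. What does the date do?** The text allows two readings.
- *Order.* The date sets the sequence in which patients take successive places on the permuted-block list. The block sentence and the word *randomly* in section 6.1 make this the likelier reading.
- *Arm.* The date itself selects the arm.

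The order reading still leaves a gap. Section 6.3 lets a patient skip screening tests already done within 30 days, so the time from baseline visit to confirmed eligibility can differ between patients. Someone screened later may be cleared first. If order follows the baseline date, her place depends on the unresolved status of the earlier patient. The protocol does not say whether a place is held, skipped or reassigned.

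**Step 3. When does randomisation happen?**

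| Section | Order given |
|---|---|
| 3.2 | consent, study code, randomisation |
| 6.1 | consent and eligibility, then randomisation |
| 6.3 | consent, screening tests, eligibility confirmed, randomisation |

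Sections 6.1 and 6.3 agree. Section 3.2 does not show the screening step.

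**Step 4. How large could it be?** The protocol does not fix the size, so only a range can be given.
- Date only orders patients, the list is concealed, and release follows eligibility: the date link adds no foreknowledge.
- Date indexes an accessible list or decides the arm: up to 40 of 40 allocations could be known in advance.
- Section 3.2 followed literally: each patient excluded after allocation is 1/20 = 5% of an arm and 1/40 = 2.5% of the trial. The protocol gives no expected number of screen failures.

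**Step 5. What part comes from the blocks alone?** A simulation of 20,000 lists of 40 patients used blocks of 4 and 6. It assumed that both sizes are equally likely and that the guesser sees every past allocation. Guessing the arm with fewer patients so far, with a coin flip on ties, was right about 69% of the time, against 50% by chance. About 5.6% of allocations were certain to someone who also knew the possible sizes. Visit date plays no part in this calculation.

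**The case against.** The strongest defence is that section 6.1 should be read whole. It prescribes random permuted blocks and assigns only patients who are eligible and have consented, which matches section 6.3. On that reading the date is loose wording for order of entry, a screen failure is never assigned, and section 3.2 is a shortened recruitment outline. Most of this stands, and it rules out several stronger readings that a reader might infer:

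- *Allocation is predictable as planned.* The documents do not establish this. It depends on an accessible list or on the date deciding the arm, and the protocol states neither.
- *Screen failures use up block places and intention-to-treat is broken.* This follows only if section 3.2 is taken literally, or if places are reserved by screening date.
- *The 69% guess rate measures the harm of the date link.* It does not. It comes from small blocks with known past allocations, and removing the date would leave it unchanged.
- *Staff choose the baseline date, or the same clinicians recruit, treat and score.* The protocol does not say who schedules the visit. Consent is taken by a study team member, titration lies with rheumatologists, and the M-score with the attending professional. Only the surgeons' overlap between eligibility and response assessment is stated.

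Accrual also limits steering by date. At 10 to 15 patients a year (10/12 = 0.8 to 15/12 = 1.25 a month), there will often be no second candidate to take an unwanted place. The same slow pace makes past allocations easy to remember.

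The defence does not explain what the date is for, supply a concealment step, or reconcile section 3.2 with section 6.3.

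**Conclusion.** The point holds as an ambiguity and a contradiction in stated text. Section 6.1 keys assignment to a date that precedes eligibility and does not say how the date is used. Sections 3.2 and 6.3 place randomisation at different points. In an open-label, single-centre trial where surgeons judge eligibility and assess response, this leaves an avoidable route to selection at entry, conditional on the date indexing an accessible list. It also leaves a route to exclusion after allocation, conditional on section 3.2 being followed.

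No numerical bias can be assigned; the range runs from none to full foreknowledge. The conclusion assumes that no concealment procedure is laid down elsewhere. If one exists in a document not shown, the remaining defect is the wording of section 6.1 and the conflict with section 3.2. The protocol should be corrected, because the defect concerns entry to the trial and cannot be dealt with at analysis.

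**What to change.** 1. In section 6.1, delete the phrase that ties assignment to the baseline visit date. State instead that the next allocation on a concealed permuted-block list, not accessible to recruiting staff, is released only after all screening results confirm eligibility.
2. In section 3.2, insert screening and confirmed eligibility between the study code and randomisation, so that the order matches section 6.3.
3. Optionally, move the "randomly varying block sizes of 4 and 6" to a document that recruiting staff do not hold. This removes the few allocations that knowledge of the sizes makes certain. It does not stop guessing from running totals.

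The cost is a wording amendment and minor set-up for concealed release. REDCap is already used for recruitment data and could serve if its randomisation module is available, which the protocol does not say. Otherwise someone outside the recruiting team would need to hold the list. Sample size, visits and analysis are unaffected.

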| Figure 1 below shows the study timeline for prednisolone and methrotexate treatment arm.  Figure 2 shows the drug dosage and schedule.  **Figure 1: Study Timeline for Prednisolone and Methotrexate Treatment Arm**   \| **Prednisolone/Methotrexate** \| \| **Study period (1 year)** \| \| \| \| \| \| \| \| --- \| --- \| --- \| --- \| --- \| --- \| --- \| --- \| --- \| \| **Phases** \| \| **Screening** \| **Treatment phase** \| \| \| \| **Follow-up phase** \| \| \| **Time point** \| \| Baseline \| T_0_ \| T_1_ \| T_2_ \| T_3_ \| T_4_ \| T_5_ \| \| Day 0 \| 1^st^  Month \| 2^nd^  Month \| 3^rd^  Month \| 6^th^  Month \| 12^th^  month \| \| Assessment \| Window Period (Day) \|  \| ±7 \| ±14 \| ±14 \| ±14 \| ±14 \| ±30 \| \| Clinical Visit \| X \| X \| X \| X \| X \| X \| X \| \| Blood Test for  FBC/LFT/RP \| X \|  \| X \| X \| X \| X \|  \| \| Blood Test for  Anti-HBc/Anti-HCV/HBsAg/ Serum Beta-HCG pregnancy test ^1^ \| X \|  \|  \|  \|  \|  \|  \| \| Additional Blood for Research \| X \|  \| X \|  \|  \| X \|  \| \| Chest X-Ray ^2^ \| X \|  \|  \|  \|  \|  \|  \| \| Starting Dose \|  \| X \|  \|  \|  \|  \|  \| \| Dose Assessment \|  \|  \| X \| X \| O \|  \|  \| \| Breast Ultrasound \|  \|  \|  \|  \| X \| O \|  \| \| Surveys \|  \| X \|  \|  \|  \|  \| X \|   X= compulsory procedure O=procedure depending on the doctor’s discretion   1. Blood tests (Anti-HBc/Anti-HCV/HBsAg) will be exempted if patient has done the same test within 30 days. 2. Chest X-Ray will be exempted if patient has done the same test within 30 days.   **Figure 2: Flowchart of the treatment schedule for prednisolone and methotrexate during the treatment phase.**  [figure not shown] |  |
| **STUDY DESIGN** |  |
| Summary of Study Design |  |

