| **UPIRTSO events** refers to problems, in general, to include any incident, experience, or outcome (including adverse events) that meets ALL of the following criteria:   1. **Unexpected** 2. Pregnancy   In the event that the patient becomes pregnant during the study period, although very unlikely (patient will be screened for pregnancy before treatment phase and checked for pregnancy status at each clinical visit), patient will be withdrawn from the trial immediately. However, patient will be advised by their doctor or study investigator(s) on the procedures to stop medication.   1. Cancer   In the event that the patient is diagnosed with cancer during the study period, patient will be withdrawn from the trial immediately. However, patient will be advised by their doctor or study investigator(s) on the procedures to stop medication.   1. Fall risks   In the event that the patient falls during the treatment phase due to the side effect, doctor or study investigator(s) will assess and evaluate the severity of the fall before advising on the continuation of the study drug.  Expedited reporting to the IRB will be done as soon as possible, and not later than 7 calendar days after first knowledge by study investigator(s).   1. **Related or possibly related to participation in the research**   Prednisolone may cause mood changes (confusion, depression), weight gain, fluid retention, nausea, vomiting, indigestion, easy bruising, blood or black, tarry tools, blurred vision, increased urination or thirst, muscle weakness or cramps and severe stomach pain.  Methotrexate may cause mouth ulcers, nausea, vomiting, abdominal pain, diarrhoea, rash, hair loss, easy bruising, severe sore throat, tiredness, paleness, yellow eyes, tea-coloured urine, constant abdominal pain, risk of infection and breathlessness or persistent dry cough.   1. **Risk of harm**   Both prednisolone and methotrexate have been widely used clinically for treatments of other diseases and have a good safety profile.  The study investigators will make every effort to mitigate risks and ensure that the inclusion and exclusion criteria are strictly adhered to. Study investigators will also conduct close monitoring on the patients’ well-being during the clinical visits.  **Reporting Timeline for UPIRTSO Events to the NHG DSRB.**   1. Urgent Reporting: All SAE(s) listed whether related to or not to the study will be reported to IRB within 24 hours after first knowledge by study investigator(s):  - Results in death. - Is life-threatening (immediate risk of death). - Requires inpatient hospitalization or prolongation of existing hospitalization. - Results in persistent or significant disability/incapacity. - Is a medically important event.  1. Expedited Reporting: All collected study AE(s) will be reported as soon as possible, but not later than 7 calendar days after first knowledge by the study investigator(s). |  |

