| Patients who consented to the study would have to undergo a few laboratory tests and procedures at the baseline visit to ensure that they meet the inclusion and exclusion criteria. One of the safety precaution tests conducted would be a pregnancy test to ensure that patient is not pregnant before consumption of drugs from either arm. The drugs used in this trial may impair fetal development, if patient is pregnant.  Methotrexate may occasionally lower blood count and cause liver inflammation. To detect these symptoms early, patients under the methotrexate arm is required to undergo a blood test on the 1^st^ (T_1_), 2^nd^ (T_2_), 3^rd^ (T_3_) and 6^th^ (T_4_) month. If an increase in dosage in methotrexate is required by the doctor, patients will continue to undergo a blood test as per doctor’s request.  An independent data monitoring committee which composes of biostatistician and clinical experts will be established to monitor the study progress, compliance, and data governance. The committee will meet on regular basis and will be responsible for independently evaluation of the safety for the patients participating in the clinical trial. Recommendation and concerns will be made by the committee for the study conduct and enrolment. In addition, the committee will regularly review the study Adverse Events (AEs) and Serious Adverse Events (SAEs). Investigator will be responsible to report relevant AE and SAE to the ethic board (DSRB and HSA) in accordance with the reporting requirement. |  |
| Complaint Handling |  |
| On the Informed Consent Form, there will be a contact number given that patient can raise their concerns to. A team will be designated to address the compliant, if any. All complaints will be kept anonymous. |  |
|  |  |
| **DATA ANALYSIS** |  |
| Data Quality Assurance |  |
| NUHS REDCap will be used to capture recruitment and relevant clinical data. The data will be routinely checked by study coordinators and study team members for accuracy and completeness of data. This IT system complies with applicable institutional data security, privacy, confidentiality, integrity and quality at NUHS cluster. FormSG will be used for the pre-treatment and post-treatment online surveys to capture patient related outcome measures. |  |
| Data Entry and Storage |  |

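### Section 6.3 and Figure 1 footnote 1 disagree on whether the screening pregnancy test may be waived, and the per-visit pregnancy check claimed in Section 9.2 is not scheduled

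*Protocol*

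**What the plan says.** Five places in the protocol bear on this.

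- **Section 6.3, Screening.** It describes "a baseline blood test (32mls, including pregnancy test, Hepatitis B test, Hepatitis C test, full blood count, liver function test and renal function test") plus a chest X-ray, done at baseline to establish eligibility. The same paragraph then says: "Patient may be exempted from chest X-Ray and/or blood test if patient has done the same test within 30 days". No component of the blood test is excepted.
- **Section 4, Figure 1, footnote 1.** "Blood tests (Anti-HBc/Anti-HCV/HBsAg) will be exempted if patient has done the same test within 30 days". The footnote marker is attached to a combined row that lists the three hepatitis markers and ends with "Serum Beta-HCG pregnancy test ^1". The separate row for blood count, liver and renal tests carries no marker.
- **Section 4, Figure 1, schedule.** Beta-HCG is marked once, at baseline. T0, where the starting dose is marked, has no blood test of any kind.
- **Section 9.2, pregnancy entry.** Pregnancy during the study is called very unlikely because "patient will be screened for pregnancy before treatment phase and checked for pregnancy status at each clinical visit".
- **Section 9.4, Safety Monitoring Plan.** The baseline precautions include "a pregnancy test to ensure that patient is not pregnant before consumption of drugs from either arm", and the reason follows: "The drugs used in this trial may impair fetal development, if patient is pregnant".

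**The concern.** Current pregnancy is an exclusion criterion (Section 3.4), and the protocol itself names a fetal risk from the trial drugs. Whether the test that enforces the exclusion is always done at baseline, or may be replaced by an earlier result, should therefore have one answer. A site reading Section 6.3 and a site reading the words of footnote 1 would act differently for the same woman.

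The population is women aged 21 to 60, and the background section describes patients as usually in their reproductive years. At stake is a woman who conceived after an accepted earlier test, or too shortly before it to be detected, and who then starts a study drug without a new test. Section 9.2 offers a further safeguard, but a site working from Figure 1 and the visit descriptions would find no instruction to carry it out.

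**Working it through.** No sample size, power or event figure is involved. The check sets the passages side by side; the only arithmetic is the possible age of the pregnancy result.

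**Step 1. Which screening tests may be waived for a result from the previous 30 days?**

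| Test | Section 6.3 | Figure 1 |
| --- | --- | --- |
| Hepatitis B and C serology | Yes | Yes (footnote 1) |
| Pregnancy test (beta-HCG) | Yes, read literally | Not named in footnote 1, but its row carries the marker |
| Blood count, liver, renal | Yes, read literally | No marker on the row |
| Chest X-ray | Yes | Yes (footnote 2) |

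The two places agree on hepatitis serology and the chest X-ray. They differ on blood count, liver and renal tests. On the pregnancy test they differ if the footnote's words govern and agree if its marker governs, so Figure 1 is itself ambiguous there. Section 6.3 names the research sample separately, so its exemption is naturally read as covering the eligibility set just defined.

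**Step 2. How old can the qualifying pregnancy result be at first dose?**

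Inputs: maximum age of an accepted result, 30 days (Section 6.3, taken as counted back from the baseline visit, since no anchor is given); T0 visit window, ±7 days (Section 6.3 and Figure 1). The interval from baseline to T0 is not stated. Assumption: it is 0 to 7 days, which treats the window as the interval.

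Age at first dose = age at baseline + interval from baseline to T0.

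- Section 6.3 read literally, oldest accepted result: 30 + 0 = 30 days to 30 + 7 = 37 days.
- Footnote 1 by its words, test done at baseline: 0 + 0 = 0 days to 0 + 7 = 7 days.

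On the same assumption, the two readings can therefore differ by up to 30 days. A longer interval to T0 would add equally to both.

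**Step 3. Is a later check scheduled?**

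Figure 1 marks seven clinical visits (baseline and T0 to T5). None after baseline carries a pregnancy item, and the visit descriptions in Section 6.3 mention none. Section 9.2 taken at its word would require a status check at T0, because T0 is a clinical visit, but it gives no method.

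**Step 4. Does this fit the stated purpose?**

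Section 9.4 says the test is there to establish that the woman is not pregnant before she takes either drug. A result that predates baseline cannot show that for a pregnancy begun after the test.

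**The case against.** The strongest reply is that the specific text should govern the general. Footnote 1 lists the waivable blood tests and omits beta-HCG, and Section 9.4 describes consented patients as having to undergo baseline laboratory tests, with the pregnancy test among them. On that reading the pregnancy test is never waived. This is a reasonable account of the intention, and it means a reader should not infer that the protocol has settled on allowing the waiver. It does not remove the defect: Section 6.3 then states the rule wrongly, and the footnote marker still sits on the pregnancy row.

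Other safeguards exist. Section 6.2 bars women who report a pregnancy or test positive at recruitment, Section 6.3 has plans for pregnancy reviewed beforehand, and Section 8.4 tells patients not to become pregnant. These lower the risk, but none detects an unrecognised pregnancy.

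Three stronger readings are tempting and are not supported:

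- **One test against seven promised.** Section 9.2 promises a check of status, not a test. Asking the patient might satisfy it, and T5 may be a teleconsultation. Absence from Figure 1 is also limited evidence, since the M-score has no row there either; but Section 6.3 does place the M-score at clinical visits, and it does not do so for the pregnancy check.
- **The result will be at least a menstrual cycle old.** Thirty days at baseline is the maximum that the waiver allows, not the typical age.
- **Month-old liver, renal or blood count results are inadequate.** No passage says so. The documents show only that Section 6.3 and Figure 1 differ on whether these tests may be waived.

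**Conclusion.** The contradiction is certain; the harm is a possibility. Section 6.3 and Figure 1 footnote 1 give different lists of waivable screening blood tests, and the status of the pregnancy test cannot be settled from the text. Under the literal wording of Section 6.3, the qualifying pregnancy result may be up to 30 days old at baseline and up to about 37 days old at first dose. The second figure rests on assuming 0 to 7 days from baseline to T0, and both count the 30 days back from baseline. With no blood test at T0, an unrecognised pregnancy could be missed, contrary to the purpose stated in Section 9.4. The per-visit check relied on in Section 9.2 has neither a place in the schedule nor a method.

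How many of the planned 40 patients would be affected cannot be derived, because the protocol does not say how many would arrive with a recent test. The point still needs correcting, because it decides how an exclusion criterion linked to a stated fetal risk is applied. A reader might infer that the protocol knowingly admits pregnant women; it does not, since Sections 3.4, 6.2 and 9.4 all aim to keep them out.

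**What to change.** Reconcile Section 6.3, Figure 1 with its footnote 1, Section 9.2 and Section 9.4:

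1. Keep one list of the screening tests that may be replaced by a result from the previous 30 days. Say explicitly whether the pregnancy test and the blood count, liver and renal tests are on it, and use the same list in Section 6.3 and Figure 1.
2. Place the footnote marker only on the tests to which it applies, splitting the combined hepatitis and beta-HCG row if needed.
3. Show the pregnancy status check of Section 9.2 in the schedule with its method, or remove the statement and the reassurance drawn from it.

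Which tests may be waived, and when and how pregnancy status is checked, is the sponsor's clinical decision; the passages have only to agree with each other and with the purpose in Section 9.4.

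The cost is protocol wording and possibly a few extra pregnancy checks. Figure 1 already has blood draws at baseline and T1 to T4, but none at T0 or T5, so a blood-based check at either of those visits would need a new draw.
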